**Fig. 2 Fig2:**
[figure not shown]
Progression model for loaded sit-to-stand exercise (STAND). *STS* sit-to-stand, *8–12 RM* 8–12 repetitions maximum (a zone in which muscular fatigue should be reached)

**Fig. 3 Fig3:**
[figure not shown]
Progression model for loaded heel raise. *8–12 RM* 8–12 repetitions maximum (a zone in which muscular fatigue should be reached)

#### STAND

Each training session will begin with the sit-to-stand exercise. The patient will be asked to sit in a standard chair with armrests with a seat height of approximately 45 cm. The chair is placed so that it cannot slide during the exercise. The patient is to keep the feet on the floor at shoulder width and to cross the arms at the wrists with the hands placed on the opposite shoulder. The starting point in STAND is level 5 (Fig. 2). The patient will be asked to rise to a fully extended position and to sit down at a constant pace and will be verbally encouraged by the supervising physiotherapist to perform as many repetitions as possible, maintaining the same pace to ensure training to contraction failure [69]. If the patient is able to perform more than 12 repetitions he/she will progress to the next level (level 6), performing the exercise wearing a weight vest (Titan Box, 1–30 kg) containing the number of kg required to reach 8–12 RM, and so forth. If the patient is not able to perform eight repetitions at level 5, regression is permitted (to level 4) allowing the patient to use the armrests in the concentric phase, and so on.

#### Heel raise

The progression of the heel raise exercise will follow the progression model for heel raise (Fig. 3). The patient will be asked to stand behind a standard chair keeping the hands lightly on the back of the chair for balance support. The patient is asked to keep the feet on the floor at shoulder width. The starting point in the progression model is level 4 (Fig. 3). The patient will be asked to lift both heels to stand on the forefeet and to lower their heels to a standing position at a constant pace. The patient will be verbally encouraged by the physiotherapist to perform as many repetitions as possible, maintaining the same pace to ensure training to contraction failure [69]. If the patient is able to perform more than 12 repetitions he/she will progress to the next level (level 5), performing the exercise wearing a weight vest (Titan Box, 1–30 kg) containing the number of kg required to reach 8–12 RM, and so forth. If the patient is not able to perform eight repetitions at level 4, regression is permitted (to level 3) allowing the patient to use the back of the chair as support in the concentric phase, and so forth.

#### Protein supplement

In this study, protein is considered as an integral part of strength training to optimize the anabolic response after training. Therefore, immediately after each training session the patient will be asked to consume an oral protein supplement (Nutridrink Compact Protein from Nutricia A/S) containing 18 g milk-based protein and 300 kcal.

### Standardization of intervention

The primary investigator will perform pre-intervention meetings with all involved physiotherapists to ensure standardization of the intervention. At the meetings, the physiotherapists will be introduced to the warm-up program and the strength training protocol. At the meeting, the strength training exercises will be performed by all involved physiotherapists to ensure common knowledge about the requirements at each level of the program. A laminated version of the warm-up program as well as the progression models for both strength training exercises will be provided to all involved physiotherapists. During the study period, the physiotherapists will be able to contact the primary investigator or a study nurse at all times should any questions arise. If a physiotherapist leaves the project, e.g. in the case of leave of absence or ending employment, the primary investigator will ensure that the physiotherapist taking over will be introduced to the protocol in the same manner as the physiotherapists who are already involved.

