### Blinding

To ensure concealment of allocation, a study nurse will be in charge of the randomization procedure following the randomization list which will not be available to the investigators. If a patient is randomized to the intervention group, the study nurse will inform the involved physiotherapists about this allocation. Patients will be asked not to reveal to the investigators to which group they belong. The discharge test in the patient’s home will be conducted before the first post-discharge training session to avoid the investigator seeing the exercise equipment in the home. Moreover, 4-week follow-up assessments will take place between 4 and 5 weeks after discharge, and the study nurse will inform the investigators when patients are ready for the 4-week follow-up assessment (end of intervention) regardless of allocation, to avoid the investigators guessing who belongs to which group. Also, all training equipment will be removed from the patients’ homes before the 4-week assessment to ensure that the investigators do not see the equipment in those homes. Additionally, all contacts with physiotherapists in the hospital and in the municipalities regarding allocation, questions about the protocol and other practicalities will be undertaken by the study nurse to ensure blinding of the investigators. In the case of a possible adverse event and the unavailability of one of the co-authors to evaluate the severity of the event, the allocation of the patient can be revealed to the investigators in order to assure proper treatment of the patient. If the patient can no longer participate in assessments he/she will be excluded from the study. Otherwise, the patient will remain in the study and all information of all such events will be reported in the manuscript.

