### Primary outcome measure

The primary outcome will be change in the DEMMI score from baseline to 4 weeks after discharge (end of intervention, primary end point). The DEMMI is a valid and reliable measure of mobility in both acute and subacute older medical patients and in community-dwelling older adults [62, 72–74], and can be used to accurately monitor mobility in older adults [72]. It includes observations ranging from mobility to dynamic balance and is scored on a scale from 0 to 100 with 100 representing the highest level of mobility [72, 73], and with a minimal clinically important difference of 10 points for acute older medical patients [72].

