### Data collection

The primary investigator and a team of three assistant investigators will perform all baseline and follow-up assessments. All four investigators are trained physiotherapists with 1 to 15 years of experience.

The admission assessments will be performed on the acute medical admissions ward or on an internal medicine ward at Copenhagen University Hospital, Hvidovre, Denmark, within the first 48 h after admission. All follow-up assessments will be performed in the patient’s own home, and the same investigator will assess the same patient at all assessments whenever logistically possible, to promote patient retention.

During each training session the supervising physiotherapist will complete an exercise diary consisting of information about the level of exercise attained according to the progression models, the extra load added (kg), and the number of sets and repetitions performed at each level. Self-reported pain will be registered immediately before and after each training session by the use of the VRS. Moreover, the physiotherapist will register reasons for non-participation as well as the amount of protein consumed after each training session. The patient time line including data collection is presented in Table 3.

**Table 3 Tab3:** Patient timeline

	Study period						
Time point	Admission	Baseline	Hospital intervention	Discharge assessment	Home intervention	4-week assessment	6-month assessment
		≤48 h after admission	Daily during hospitalization	In patient’s home	3 times per week for 4 weeks in patient’s home	In patient’s home	In patient’s home
Enrollment							
Eligibility screen	X						
Informed consent	X						
Study groups							
Strength training		X	X	X	X	X	X
Control		X		X		X	X
Assessments							
Baseline assessment^a^		X					
Primary outcomes		X		X		X	X
Secondary outcomes		X		X		X	X
Descriptive variables and possible confounders and modifiers		X		X		X	X

^a^See Table 2 for a detailed description of assessed variables

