### Data management

All case report forms will be checked for errors and missing data before being archived in a study database and all paper-based versions will be locked in a filing cabinet to ensure confidentiality. The primary investigator will have access to the full dataset, in which no information about allocation is visible, and co-investigators will have access as needed. Data management will comply with the rules of the Danish Data Protection Agency. The full protocol will be published, and public access to de-identified patient-level data will be provided once the data have been analyzed. All data will be double entered in Epidata Entry 3.1 (Epidata Associations, Odense, Denmark), range checked for data values, checked against the paper-based assessments and exported to SAS Enterprise Guide 6.4 (SAS Institute Inc., Cary, NC, USA). Data from the *activ*PAL3™ will be downloaded to a computer using *activ*PAL™ Professional Software, version 7.2.32. For each *activ*PAL3™ monitoring the investigators will note the time and date that the monitor is attached to the patient, the time and date that monitoring is started, when the monitor is removed from the patient, and reasons for not wearing the monitor if it is removed prematurely.

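### Physiotherapists may take in-study questions to the primary investigator, an outcome assessor; this contradicts the blinding rule and opens a route to unblinding

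*Protocol article*

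**What the plan says.** Four parts of the protocol article bear on this point.

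- **Blinding.** The nurse-only rule covers "all contacts with physiotherapists in the hospital and in the municipalities regarding allocation", and the sentence continues: "questions about the protocol and other practicalities will be undertaken by the study nurse to ensure blinding of the investigators". The same section says: "If a patient is randomized to the intervention group, the study nurse will inform the involved physiotherapists about this allocation".
- **Standardization of intervention.** For the study period, "the physiotherapists will be able to contact the primary investigator or a study nurse at all times should any questions arise".
- **Data collection.** "The primary investigator and a team of three assistant investigators will perform all baseline and follow-up assessments". To help retention, "the same investigator will assess the same patient at all assessments whenever logistically possible".
- **Data management.** "The primary investigator will have access to the full dataset, in which no information about allocation is visible". The primary investigator is therefore meant to be blind, in the data as well as at the visits.

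On the primary outcome, the DEMMI, the Primary outcome measure section says: "It includes observations ranging from mobility to dynamic balance and is scored on a scale from 0 to 100".

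**The concern.** The trial is described as investigator-blinded. Patients know which group they are in and are only asked not to tell. Protection of the primary end point therefore depends heavily on the person who scores the DEMMI at 4 weeks not knowing the arm.

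The Blinding section takes trouble over much weaker cues. Equipment is removed from the home before the 4-week visit, the discharge test precedes the first home session, and the nurse announces that a patient is ready for the 4-week visit in the same way for both arms. A direct line from the treating physiotherapist to one of the assessors works against that care.

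A disclosure would concern patients in the intervention arm, so any resulting shift in scoring would affect one arm only. The planned mixed model with multiple imputation could neither detect nor correct it.

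**Working it through.** The check is mainly textual.

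1. **Same subject, different instruction.** The Blinding section names questions about the protocol and practicalities, not only allocation, and gives blinding as the reason for sending them to the nurse. The Standardization section covers any question, at any time in the study period, and offers the primary investigator as an alternative to the nurse. A physiotherapist who follows the second instruction can break the first.
2. **The contact is an assessor.** Data collection places the primary investigator among the four people who do all baseline and follow-up assessments.
3. **How a question discloses the arm.** The nurse informs physiotherapists when a patient is allocated to the intervention. Exercise level and added load are decided set by set for each patient (Training intervention, STAND and Heel raise sections), so patient-specific questions are foreseeable. A question about training an identifiable patient under the protocol implies the intervention arm.
4. **Carry-over.** Keeping the same assessor for a patient where logistics allow means that a disclosure during the hospital or home phase can reach the 4-week visit.
5. **Exceptions.** The Blinding section lets allocation be revealed to investigators only for a possible adverse event when no co-author is available to evaluate it. Routine questions fall outside that.

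**Can the size be worked out?** Let *s* be the share of intervention-arm 4-week assessments done by the primary investigator, *p* the proportion of those patients whose allocation has been disclosed, and *d* the average scoring drift in DEMMI points for a disclosed patient. Then

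shift in the between-group difference = *s* × *p* × *d*.

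The article gives none of the three. The values below are assumptions that show the range and are not estimates.

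- *s* = 0.25 to 0.50, *d* = 3 to 5, *p* = 1 (every such patient disclosed): 0.25 × 1 × 3 = 0.75 to 0.50 × 1 × 5 = 2.5 points, or 7.5% to 25% of the 10-point target.
- Same *s* and *d*, *p* = 0.10 to 0.20: 0.25 × 0.10 × 3 = 0.075 to 0.50 × 0.20 × 5 = 0.5 points, or 0.75% to 5% of the target.

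To express this as type I error, take the planning figures in the Sample size section: SD 12.8, 27 per arm, two-sided 5%. These reproduce. The normal approximation gives 2 × (1.96 + 0.84)² × 12.8² / 10² ≈ 25.7, so 26. The exact *t* test gives 26.7, so 27, with power 80.4%. With no true effect, the *t* statistic has 52 degrees of freedom and noncentrality (shift / 12.8) × √(27/2). This gives:

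- shift 0.5 points: type I error about 5.2%
- shift 0.75 points: about 5.5%
- shift 2.5 points: about 10.9%

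The answer runs from negligible to material, depending on quantities that the article does not state. The sample size itself is unaffected.

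**The case against.** The strongest reply is that the sentence sits in a section about standardizing the warm-up and the progression models, and is probably a drafting leftover. Disclosure needs three things together: a question about an identifiable patient, put to the primary investigator rather than the nurse, about someone whom that investigator assesses. A query about vest loading in general, or about what a level requires, reveals nobody's arm. The pre-intervention meetings, and the introduction of a replacement physiotherapist, identify no patient. The other safeguards in the Blinding section are sound.

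Most of this stands, and it limits the point to a possible route to unblinding one of four assessors. It does not remove the conflict, because the Blinding section does not separate technique from allocation and sends both to the nurse.

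A reader might infer more than the documents support:

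- **That the plan itself unblinds the assessor.** It opens a channel. Whether anyone learned an allocation through it is not stated.
- **That the physiotherapists treat intervention patients only.** This is not stated. They were recruited from the medical wards and municipal geriatric rehabilitation, and routine care may include exercise, so they may meet control patients too. What reveals the arm is a question about training a particular patient under the trial protocol.
- **That assessors encourage patients during the strength tests.** Verbal encouragement is described only for the training sessions, given by the physiotherapist.
- **That assessor blinding is the only blinding.** Allocation is also hidden in the dataset.

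**Conclusion.** The contradiction is real, and no other part of the article resolves it. As written, the plan lets a treating physiotherapist put a patient-specific question to someone who may go on to score that patient's primary outcome.

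The conclusion rests on three things that the article states: the two conflicting contact rules, the primary investigator's role as assessor, and the nurse's notification of intervention allocations. It does not rest on a numerical bias. Reading the 0.75 to 2.5 point range as the likely effect would be unjustified, because it assumes that every intervention patient assessed by the primary investigator has been disclosed. The size stays unknown without that investigator's share of assessments, the frequency of patient-specific questions and the scoring drift.

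The point deserves correction because it touches the blinding of an observed primary outcome and costs almost nothing to put right.

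**What to change.** 1. In Standardization of intervention, remove the primary investigator as a contact during the study period, so that all in-study questions go to the study nurse, in line with the Blinding section. Where the nurse needs technical advice, the nurse relays the point without identifying a patient. The pre-intervention meetings can stay as they are.
2. Add a rule to Blinding and Data collection: if an investigator learns a patient's allocation, one of the other existing investigators does that patient's remaining assessments. This overrides the preference for the same assessor, and the event is logged.
3. Recruitment is already under way (Study status), so a change of wording cannot undo past calls. Record which contact channel has been used so far and any disclosures already made, and report both with the results.

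The cost is a small text change and an instruction to the physiotherapists, two in hospital and five at home according to the Training intervention section. No new staff are needed, and sample size and analysis do not change. The downside is slower answers to technical questions and an occasional change of assessor, with some loss of the continuity meant to help retention.

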### Outcome measures

Outcomes measures will be assessed on admission (baseline), shortly after discharge, approximately 4 weeks after discharge (primary end point) and 6 months after discharge. All outcomes to be assessed are presented in Table 2.

**Table 2 Tab2:** Variables to be assessed

Variable	Baseline	Discharge	4 weeks	6 months
Primary outcome				
de Morton Mobility Index (DEMMI)	+	+	+	+
Secondary outcomes				
24-h mobility (*activ*Pal3™ monitors; 1-week assessments)	+	+	+	+
Isometric knee extension strength	+	+	+	+
30-sec sit-to-stand test	+	+	+	+
Habitual gait speed (HGS)	+	+	+	+
Hand-grip strength (HG)	+	+	+	+
Activities of Daily Living (Barthel Index 20)	+	+	+	+
Descriptive variables				
Age	+			
Gender	+			
Weight	+	+	+	+
Educational level	+			
Living status	+	+	+	+
History of smoking	+			
Use of ambulatory devices	+	+	+	+
Use of municipal help	+	+	+	+
History of falls during the last year	+	+	+	+
Falls Efficacy Scale	+	+	+	+
Nutritional Risk Screening (NRS)	+	+	+	+
New Mobility Score (NMS)	+	+	+	+
Cumulated Ambulation Score (CAS)	+	+	+	+
Days per week spent outdoors	+	+	+	+
Hospitalization within last 4 weeks			+	
Hospitalization within last 6 months	+			+
Possible confounders and modifiers				
Age	+			
Gender	+			
Cognition				
Short Orientation-Memory-Concentration test (OMC)	+			
Mini Mental State Examination (MMSE)		+	+	+
Trail Making Test (Trails)		+	+	+
Digit Symbol Substitution Test (DSST)		+	+	+
Hopkins Verbal Learning Test (HVLT)		+	+	+
Geriatric Depression Scale (GDS)		+	+	+
Health status (EQ-5D)	+	+	+	+
Self-rated health (EQ-5D)	+	+	+	+
Mini Nutritional Assessment (MNA)	+	+	+	+
Self-reported physical activity	+	+	+	+
Verbal Ranking Scale (VRS)	+	+	+	+
Medications	+	+	+	+
History of training before hospitalization	+			
History of training in the municipality after discharge		+	+	+

### Primary outcome measure

The primary outcome will be change in the DEMMI score from baseline to 4 weeks after discharge (end of intervention, primary end point). The DEMMI is a valid and reliable measure of mobility in both acute and subacute older medical patients and in community-dwelling older adults [62, 72–74], and can be used to accurately monitor mobility in older adults [72]. It includes observations ranging from mobility to dynamic balance and is scored on a scale from 0 to 100 with 100 representing the highest level of mobility [72, 73], and with a minimal clinically important difference of 10 points for acute older medical patients [72].

### Secondary outcome measures

Secondary outcomes will be the following six: (1) 24-h mobility measured by an *activ*PAL3™ activity monitor (PAL Technologies Ltd., Glasgow, UK). The patient will be asked to wear an *activ*PAL3™ on the thigh during hospitalization, the first week after discharge, the first week after the 4-week assessment and the first week after the 6-month assessment. The patient will wear the *activ*PAL3™ halfway between the spina iliaca anterior superior and the patella on the front side of the right thigh. The monitor will be covered in Tegaderm™ transparent waterproof film (3 M, Maplewood, MN, USA), attached to the patient by a PAL*stickie*™ (dual-layer hydrogel adhesive pad) and covered by Leukomed® T transparent film (BNS medical, Hamburg, Germany) to enable the patient to wear the *activ*PAL3™ while showering. The patient will be asked to wear the monitor for 24 h per day. The *activ*PAL3™ can record continuously for 7 days, whereafter the monitor will be replaced should the hospitalization be of a longer duration. The *activ*Pal3™ accelerometer measures time spent sitting/lying, standing and walking, the number of steps taken, cadence and the number of sit-to-stand and stand-to-sit transitions. The *activ*Pal3™ is a valid and reliable measure of posture and transitions in healthy young and mobility limited older adults [75–77] and of walking at speeds between 0.67 m/s and 1.56 m/s in young and older adults [78–80]. Unpublished data from Hvidovre Hospital regarding 317 older medical patients has shown that 46 % of them walked at speeds below 0.67 m/s, why time spent walking could potentially be categorized as standing for 46 % of older medical patients. For this reason, if 15 % of the total sample walk at speeds below 0.67 m/s the *activ*Pal3™ data will be dichotomized into sedentary (sitting/lying) and upright time (walking/standing); (2) isometric knee extension strength (IKE) in the dominant leg using a handheld dynamometer (Power Track II Commander; JTech Medical, Midvale, UT, USA). The patient will be seated in a standard chair with a seat height of approximately 45 cm, with the arms crossed over their chest and 90° knee flexion [81, 82]. A strap will be attached to the chair and the patient’s ankle, just proximal to the malleoli. A transducer will be placed under the strap and a thin foam pad will be placed between the transducer and the leg. The distance between the lateral femoral epicondyle and the center of the transducer will be measured (the moment arm). The patient will be asked to extend the leg as forcefully as possible for 5 s three times with a 1-min pause in between. Up to two additional contractions will be performed if the last contraction elicits the highest value to ensure that maximal force is measured. Isometric knee extension strength will be expressed as maximal force (Nm) per kg body weight (kg); (3) the 30-sec sit-to-stand test (STS) using a standard armchair with a seat height of 45 cm [83]. The patient will be asked to sit with the arms crossed over the chest and to stand up once without using the arms. If this is performed safely, the patient will be asked to stand up fully and sit down as many times as possible in 30 s with the arms across the chest. The number of full stands will be counted. If the patient is not able to rise once from the chair without using the arms, a modified STS will be used, allowing the patient to use the armrests for support; (4) habitual gait speed (HG) on a 4-m course [84, 85]. The patient will be asked to walk 4 m at usual pace starting from a standing position. A walking aid will be allowed if needed. The faster of two walks will be used as the outcome; (5) hand-grip strength (HGS) in the dominant hand using a handheld dynamometer (Digi-II; Saehan). The patient will be placed in a sitting position in an armchair, with the lower arm placed on the armrest, an elbow flexion of 90° and the wrist in a neutral position. The patient will be asked to place the contralateral hand on the leg with the palm facing upwards. The dynamometer handle will be set at position 2 [86] and the investigator will reset the dynamometer before handing it to the patient and will ask the patient to squeeze the handle as forcefully as possible for 5 s. The patient will be asked to perform the test three times with a 1-min pause in between. If the third test shows the highest value additional tests will be performed until performance of a lower value to ensure that the highest value possible is obtained. Hand-grip strength will be expressed in kg; (6) the Barthel Index 20 (BI) is used as a measure of Activities of Daily Living (ADL) [87]. The BI assesses the help needed in regard to grooming, toilet use, feeding, transfer, mobility, dressing, stair climbing and bathing, and in addition the presence or absence of urinary and fecal incontinence. A score of between 0 and 20 can be obtained with higher scores indicating less disability.

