After inclusion, baseline assessments will be performed whereafter the patients will be randomized to either: (1) intervention: progressive strength training during hospitalization and the first month after discharge (home-based), or (2) control: usual care. Shortly after discharge, four weeks (primary end point) and 6 months (follow-up) after discharge the patients will be assessed in their own homes. Figure 1 shows the study flow.

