### Secondary and supplementary analyses

From the primary analysis model, the effect during hospitalization and the post-intervention effect (change from 4 weeks to 6 months post discharge) will be estimated. For the secondary outcomes, similar analyses will be performed. Moreover, all analyses will be using adjustments for baseline DEMMI. To account for imbalances in in-hospital time, a sub-analysis will be performed for the effect during hospitalization and the effect from baseline to end of intervention adjusted for length of stay. Additionally, the unadjusted repeated model will be carried out following the per protocol principle, comparing patients who have fulfilled the compliance criteria with the control group. All between-group differences will be expressed as the average difference in change from baseline. The analyses outlined above will all be reported in the main trial manuscript regarding effect of the strength training program.

If additional funding is obtained, more patients will be included to increase the sample size to obtain sufficient power to model statistical interactions and perform secondary analyses (described below), which will be published subsequently. To investigate the possible influence of confounders and modifiers on the effect of the intervention on DEMMI, an unadjusted analysis of variance of the between-group change from baseline to 4 weeks post discharge in the DEMMI score will be performed. In addition, this model will be extended by adjusting for all and each of the potential confounders and modifiers one by one. Confounding effects will be evaluated by comparing the unadjusted effect of group with the adjusted effects. Moreover, to investigate whether or not the effect of the intervention is modified by the potential confounders and modifiers the adjusted models will be extended with an interaction term between group and the potential confounders and modifiers. Similar analysis will be performed with 24-h mobility (average time spent standing or walking per 24 h) and with those of the secondary outcomes that showed a significant between-group difference in the primary analysis. Also, a logistic regression with compliance as the outcome and each of the potential confounders and modifiers as covariates will be performed. All analyses will follow both the intention-to-treat and the per protocol principle.

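### The 24-h mobility baseline is a hospital recording that probably lies mostly after randomization, so change from baseline removes part of any in-hospital training effect

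*Protocol article*

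**What the plan says.** All references are to the protocol article.

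- *Secondary outcome measures*: the monitor is worn "on the thigh during hospitalization, the first week after discharge, the first week after the 4-week assessment", and again for a week after the 6-month assessment. It "can record continuously for 7 days, whereafter the monitor will be replaced should the hospitalization be of a longer duration".
- *Outcome measures*, Table 2: 24-h mobility is marked at Baseline, Discharge, 4 weeks and 6 months, and is labelled "1-week assessments".
- *Study sample and recruitment procedure*: "After inclusion, baseline assessments will be performed whereafter the patients will be randomized". *Data collection* places the admission assessments "within the first 48 h after admission".
- *Intervention group*: supervised training takes place on weekdays throughout the stay. Controls receive usual care.
- *Primary analysis for the primary outcome*: the model's responses are the discharge, 4-week and 6-month values, each minus baseline.
- *Secondary and supplementary analyses*: "For the secondary outcomes, similar analyses will be performed", and "All between-group differences will be expressed as the average difference in change from baseline". The same section takes an effect during hospitalization from this model. 24-h mobility is not exempted from any of this.

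**The concern.** A change-from-baseline contrast is a fair estimate of a treatment effect only if the baseline could not have been affected by treatment. The other five secondary outcomes are tests or scores completed at one visit, so they can be finished before randomization. 24-h mobility cannot: its Baseline value is described as a week of wear, and the only recording before discharge is the one made over the hospital stay. Part of that stay is treatment time for one arm only. Subtracting it removes from the intervention arm whatever the training did to in-hospital activity.

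At stake is the reading of the first-listed secondary outcome in the main trial report. A real gain in daily mobility could appear smaller than it is. For this outcome the effect during hospitalization would also be misnamed, because it would compare the first week at home, when home training may be running, with a recording already made on treatment.

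**Working it through.** The protocol gives no figure for 24-h mobility to reproduce. Its sample size concerns DEMMI only. It reproduces (difference 10, SD 12.8, two-sided 5 %, power 80 %: 26.7, rounded up to 27 per arm) and plays no part here.

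**Step 1. Which recording is the baseline?** Set the wear periods beside the columns of Table 2:

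| Table 2 column | Wear period |
|---|---|
| Baseline | hospital stay |
| Discharge | first week at home |
| 4 weeks | week after the 4-week assessment |
| 6 months | week after the 6-month assessment |

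No other recording could fill the Baseline column. A week of wear also cannot fit into the 48 h allowed for the admission assessments.

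**Step 2. What does the contrast estimate?** Let D be the true arm difference in a follow-up recording, H the true arm difference in hospital mobility once training has begun, and f the share of the hospital recording made after training begins. Within municipality, the arms are equal in expectation before training. The intervention arm's baseline is therefore shifted by f × H, and

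expected contrast = D − f × H.

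A simulation (200,000 patients, D = 0.6, H = 0.3, f = 0.8, in SD units) gave 0.365 against an expected 0.6 − 0.8 × 0.3 = 0.36. With a clean baseline it gave 0.605. Using the hospital recording as a covariate (correlation 0.5) gave 0.484 against an expected 0.6 − 0.5 × 0.8 × 0.3 = 0.48, so covariate adjustment reduces the bias but does not remove it.

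**Step 3. Range.** The documents give neither f nor H, so the values below are assumptions. Share of D estimated = 1 − f × (H/D). Power for a comparison that would otherwise have 80 % = Φ((1.96 + 0.84) × share − 1.96).

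| f | H/D | Share of D | Power |
|---|---|---|---|
| 0 | any | 100 % | 80 % |
| 0.5 | 0.25 | 88 % | 69 % |
| 0.8 | 0.25 | 80 % | 61 % |
| 0.8 | 0.5 | 60 % | 39 % |
| 1 | 0.5 | 50 % | 29 % |
| 1 | 1 | 0 % | no true contrast left |

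If trained patients rested more outside sessions, H would be negative and the effect overstated. With f = 0.8 and H/D = −0.25, the share is 1 + 0.2 = 120 %.

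**Step 4. How much can the exercises alone contribute?** Inputs come from *Training intervention*: three sets in a zone of 8–12 repetitions, 2 s up, 2 s down and two 1-s pauses, so 6 s per repetition.

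- Sit-to-stands: 3 × 8 = 24 to 3 × 12 = 36 per session. With weekday training, × 5/7 gives about 17–26 per day averaged over a week, if the exercise is done at a sit-to-stand level. The monitor counts these transitions.
- Time per exercise: 24 × 6 s = 2.4 min to 36 × 6 s = 3.6 min.
- Upright time: heel raises at the standing start level count in full, sit-to-stands about half (assumption). That is 2.4 + 1.2 = 3.6 to 3.6 + 1.8 = 5.4 min per session, or × 5/7 = 2.6–3.9 min per day. If the patient also stands through the two 2-min pauses between heel-raise sets, the top figure is (5.4 + 4) × 5/7 = 6.7 min per day.

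These repetitions fall in the hospital recording but not in the 4-week or 6-month recordings. *Blinding* has the equipment removed before the 4-week assessment, and the monitor goes on after it.

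**The case against.** The attachment time is not given. The monitor may well go on at the baseline visit, before randomization, and *Data management* has the investigators log when it is attached and when monitoring starts, so early hours could be separated. How monitor data become a baseline value is the kind of detail usually left to an analysis plan, which is not shown. *Additional variables* uses the first week at home, not the hospital recording, when 24-h mobility serves as a covariate, so the hospital recording is not treated as a baseline everywhere. Finally, this is one secondary outcome of six, and the expected direction is conservative.

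Much of this stands as a limit on the claim, and three stronger readings go too far:

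- *That nothing is recorded before randomization.* The text does not say so. It says only that the recording runs through the stay and defines no window that ends earlier. Some pre-training wear makes f less than 1, not 0.
- *That the bias is tens of upright minutes a day.* The stated 10–15 min session cannot be read as upright time: the warm-up is seated, there are 2-min pauses between sets, and training is on weekdays. Step 4 supports a few minutes. More would need activity induced outside the sessions, which the documents do not quantify.
- *That training could appear to lower mobility when it raised it.* This needs f × H to exceed D. None of the scenarios with positive H in Step 3 reverses the sign, so it is a worst case only.

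The objection does not remove the conflict. The article itself states a baseline, a wear period and a change-from-baseline effect measure, and together they do not fit. The planned adjustment for baseline DEMMI does not undo the subtraction, and the covariate from the first week at home is itself post-randomization.

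**Conclusion.** The point holds in limited form. As written, the plan estimates D − f × H for 24-h mobility rather than D. The bias is toward no effect if training raises in-hospital activity and reverses if trained patients rest more. Its size cannot be computed from the documents: under the assumed values in Step 3 with positive H, between 88 % and none of the true effect is estimated. The part traceable to the exercises themselves is about 17–26 sit-to-stands and roughly 3–7 upright minutes per day. The estimated effect during hospitalization for this outcome is likewise a contrast with an on-treatment recording.

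The conclusion rests on two inferences: that the hospital recording is the Baseline value of Table 2, and that most of it follows the start of training. DEMMI, its sample size and the other five secondary outcomes are not affected. This should be corrected before analysis, but it does not threaten the trial's main conclusion.

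**What to change.** For 24-h mobility, do not subtract the hospital recording. Compare the arms on absolute values in the week after discharge, the week after the 4-week assessment and the week after the 6-month assessment, adjusted for baseline DEMMI and for municipality (the allocation ratio differs between municipalities). Report the hospital recording as an on-treatment outcome in its own right, and do not label the difference between the first home week and the hospital recording as the effect during hospitalization. Correct the Baseline entry for this row of Table 2, and state the exception beside the sentence that applies the primary model to the secondary outcomes.

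The cost is a change of wording. All the data are already being collected. The downside is some loss of precision, because the comparison no longer has the patient's own earlier value of the same measure. Baseline DEMMI, measured before randomization, should recover part of it.
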